## Abstract

**Background:**

Hot flashes are the most frequent symptoms of the menopause, with 10–20% of all postmenopausal women reporting nearly intolerable occurrences. Although pharmacopuncture with hominis placenta extract is one of the new acupuncture therapies popular in East Asian medicine with a known efficacy in treating facial flushing, there has been little research on the efficacy and safety of this extract. This study, therefore, aims to evaluate the efficacy and safety of pharmacopuncture with hominis placenta extract (PLC) compared to injections of normal saline, in perimenopausal and postmenopausal women in Korea.

**Methods/design:**

This study is a randomized placebo-controlled single-blind multi-center parallel-design trial. In total, 128 perimenopausal or postmenopausal women who meet the inclusion criteria will be recruited. The treatment group will receive PLC pharmacopuncture twice a week, for a total of 18 sessions over 9 weeks. The control group will receive injections of normal saline at the same acupoints during the same period. The post-treatment follow-up assessment will occur 4 weeks after the participant has completed the treatment.

**Discussion:**

We believe that this trial will provide evidence for the efficacy and safety of PLC pharmacopuncture as a treatment for hot flashes in perimenopausal and postmenopausal women.

**Trial registration:**

Clinical Research Information Service (CRIS), Republic of Korea, ID: KCT0003533, Registered on 20 February 2019.

**Electronic supplementary material:**

The online version of this article (10.1186/s13063-019-3482-5) contains supplementary material, which is available to authorized users.

## Background

Today, women live more than a third of their lives in the perimenopausal or postmenopausal stage. Hot flashes affect their quality of life, and are usually the most common symptom, as they are experienced by 75% of women [1]. Symptoms can last from 6 months to as long as 10 years [2]. Symptoms associated with hot flashes include a feeling of intense heat, sweating, weakness, changes in heart rate, panic disorder, and anger. Repeated night hot flashes can lead to insomnia, which eventually results in difficulty in concentrating, fatigue, and cognitive impairment [3].

Although hormone replacement therapy is the most effective and popular treatment for hot flashes [4, 5], it is not administered to many women due to its adverse side effects and potential risks [6]. Recent research suggest that hormone replacement therapy increases the risk of coronary heart disease, stroke, and breast and endometrial cancer, and this has consequently resulted in increasing interest in non-hormonal therapies [7–10]. Interest has increased in phytoestrogen therapy, but its effect on menopausal symptoms remains unclear [4]. Serotonin reuptake inhibitors are effective for hot flashes but are ineffective for other menopausal symptoms [7]. Due to the varied limitations and side effects of existing treatments, research into therapies for hot flashes in complementary alternative medicine and traditional Korean medicine (including acupuncture) is receiving greater attention [11–15].

A number of clinical studies have reported that acupuncture reduces the symptoms of hot flashes. Pharmacopuncture is a combination of acupuncture and medication, and is a new therapy in which a purified herbal medicine is injected at an acupoint. It is widely used in China and Korea, and is also known as acupoint injection, herbal acupuncture, aqua acupuncture, and aquapuncture [16]. With its increasing use, various studies on pharmacopuncture have been initiated and are ongoing. However, although pharmacopuncture is used for various perimenopausal or postmenopausal symptoms, it has been the subject of very little clinical research. According to a systematic review in 2009 of randomized control trials in Korean pharmaceutical research by Park [17], the majority of such control trials on pharmacopuncture looked at musculoskeletal disorders. Thus, currently there is insufficient evidence for the use of pharmacopuncture to treat gynecological disorders such as postmenopausal syndrome.

Pharmacopuncture with hominis placenta is a widely used therapy for gynecological disorders. Hominis placenta is an extract of human placenta comprising various cell proliferators, blood clotting factors, and hormones and their precursors, such as gonadotropin, prolactin, thyroid-stimulating hormone, steroid hormones, prostaglandin, lysozyme, kininase, histaminase, erythropoietin, phospholipids, and polysaccharides [18–20]. In fact, this medicinal material has been widely used for a long time in the clinical practice of Korean gynecology, and is generally prescribed as an oral medication or pharmacopuncture [21]. Moreover, hominis placenta has mainly been used for chronic consumptive diseases or weak conditions, infertility, sexual dysfunction, and menopausal disorders. Its clinical application in pharmacopuncture is well established for infertility, menopausal disorders, freckles [22], menstrual pain [23–25], facial paralysis [26], and postpartum diseases [27].

The clinical trial drug, PLC, is manufactured from Drug Master File (DMF)-registered raw materials (hominis placenta extract) and is based on a Unicenta injection manufactured by the drug company Unimed. The hominis placenta extract has recognized efficacy in anti-oxidation, wound recovery, and anti-inflammation, and for increasing the metabolism of tissue cells [28–31]. Considering that hominis placenta pharmacopuncture is widely used to treat hot flashes in clinical practice, we are running this clinical trial using the readily available quality-controlled PLC to verify its efficacy and safety. In addition, doctors and Korean medicine doctors will work together on this clinical trial using PLC manufactured in a similar way to the licensed Unicenta injections.

## Methods/design

### Study aims

The aim of the study is to evaluate the efficacy and safety of PLC used to treat hot flashes and other symptoms of perimenopausal or postmenopausal women.

### Design and setting

This will be a randomized placebo-controlled single-blind multi-center parallel-design clinical trial. Participants will be enrolled from three hospitals: Ilsan Korean Medicine Hospital of Dongguk University, Gwangju Korean Medicine Hospital of Wonkwang University, and Dunsan Korean Medicine Hospital of Daejeon University. The study process is illustrated in Fig. 1. In accordance with the protocol, all subjects who sign the informed consent will undergo a 2-week screening period before commencing treatment. Subjects who complete the screening period and meet the selection criteria will be randomly assigned to one of two groups for 8 weeks: the treatment group, who will receive the PLC pharmacopuncture treatment, and the placebo group, who will receive injections of normal saline (NS). The relevant treatment material will be administered twice a week for 8 weeks (a total of 16 injections). From the second visit onwards, all subjects will receive a hot flash symptom diary, which they will be asked to bring to visits 4, 6, 8, 10, 12, 14, 16, and 18. The Menopause Rating Scale (MRS) will be assessed at visits 2, 10, and 18 for both groups. The post-treatment follow-up assessment will occur at visit 19, when the symptom diary and MRS questionnaires maintained by the subjects will be assessed for both groups (Figs. 1 and 2).

**Fig. 1 Fig1:**
[figure not shown]
Participant flow diagram

**Fig. 2 Fig2:**
[figure not shown]
Study time line

### Recruitment

Voluntary participants will be recruited form three centers: Ilsan Korean Medicine Hospital of Dongguk University, Dunsan Korean Medicine Hospital of Daejeon University, and Gwangju Korean Medicine Hospital of Wonkwang University. Recruitment will be through advertisements in outdoor areas, newspapers as well as on hospital websites.

### Eligibility criteria

#### Inclusion criteria

Women between 45 and 60 years of agePerimenopausal or postmenopausal women experiencing hot flashesPerimenopausal women should meet one of the following criteria:i.have a history of amenorrhea for the last 3–11 months from the consent day (visit 1)ii.have suffered irregular menstrual periods in the past 12 months from the consent day (visit 1)Postmenopausal women should meet one of the following criteria:i.have a history of spontaneous amenorrhea for the last 12 monthsii.have 6 months of spontaneous amenorrhea with serum follicle-stimulating hormone levels greater than 40 mIU/mLiii.have had a postsurgical bilateral oophorectomy with or without hysterectomy at least 6 weeks prior to the consent dayiv.have had a hysterectomyWomen having an average daily hot flash score of 10 or higher for 1 week before visit 1Subjects who agree to this clinical study after sufficient explanation

#### Exclusion criteria

Women diagnosed with psychogenic menopausal symptomsWomen suspected of having an organic diseaseWomen with severe complications of the heart, liver, kidney, or other organsWomen with a history of malignant tumorsWomen with thyroid disease or abnormal thyroid functionWomen with liver or kidney dysfunction, indicated by values of sGOT, sGPT, bilirubin, or serum creatinine over twice the normal levelWomen who may have difficulties in participating in this trial due to any of the following diseases: uncontrolled hypertension, diabetes with complications or under control with insulin injections and pumps, thyroid disease including those taking medication for thyroid disease, acute hepatitis or hepatocirrhosis, severe hyperlipidemia, neuropathic disorders, severe cardiovascular disorders, tuberculosis, and other infectious diseasesWomen with a history of hypersensitivity to hominis placenta or other drugs and food, or any other allergic disease that requires treatmentWomen who have been administered hormones or hormone analogues, except estrogen or progestin, within the past 1 monthWomen who have participated in another clinical trial within the past 3 monthsWomen who do not complete the required washout period for previous medication, such as Korean medicine treatment or other complementary medicine, that may affect perimenopausal or postmenopausal symptoms (Table 1)Women who were previously taking estrogen or estrogen/progestin (except those who complete the washout period)Women who have taken antidepressants in the last monthWomen with any illness that is determined incompatible with the acupuncture treatmentWomen with inflammation or a scar in the treatment areaNight-shift workersWomen who are unable to fill out the study documentsAny woman whom a researcher deems to be unsuitable for this trial

**Table 1 Tab1:** Washout periods

Therapy	Washout period
Hormone agents vaginally (e.g. ring, cream, gel, etc.)	≥ 1 week
Transdermal agents containing estrogen-only or estrogen/progestin	≥ 4 weeks
Oral estrogen or progestin	≥ 8 weeks
Intrauterine progestin	≥ 8 weeks
Progestin implants or a single estrogen injection	≥ 12 weeks
Estrogen pellets or progestin injections	≥ 24 weeks
Acupuncture or moxibustion	≥ 1 week
Herbal medication or pharmacopuncture	≥ 3 weeks

### Interventions

For all subjects in the pharmacopuncture group, 0.5 cc of PLC will be injected twice weekly at four acupoints (CV4, CV6, and bilateral Ex-BB1) using a 1-cc 30-gauge disposable syringe. Needle insertion will be to a depth of up to 8 mm. The control group will be injected with NS at the same points using the same technique. After the procedure, participants will receive infrared irradiation at a distance of 30 to 60 cm for 20 min so that they feel warmth in their lower abdomen. No treatments other than the prescribed treatment should be received during the test period. The pharmacopuncture treatment will be administered by an experienced Korean medicine doctor who has had at least 6 years of regular Korean medicine university education and is licensed by the Korean Ministry of Health and Welfare.

The drug for this clinical trial, PLC, is an extract of hominis placenta and will be manufactured by pharmaceutical company Unimed (Seoul, Republic of Korea). Hominis placenta is isolated from healthy pregnant women after delivery, and will be subjected to sterilization and hydrolysis extraction procedures. PLC is manufactured in accordance with Korean good manufacturing practice. The NS for the control group consists of sodium chloride 180 mg/20 ml (0.9%) and will be procured from Daihan Pharm Co. (Seoul, Republic of Korea). A researcher will label the two test materials as PLC and NS.

### Randomization

Eligible participants will be randomized into one of the two groups via stratified block randomization at the hospital where they first come into contact with the research coordinators. The stratification factor is the hospital. A separate randomization sequence will be generated by computer at the central coordinating center by an independent statistician. The randomization codes will be sealed in opaque envelopes. Randomization plans will be kept confidential, except for emergencies. In the event of adverse events and emergencies related to the safety of the subjects, the test conductor in charge can identify the assigned treatment group of the subject through the statistician, who will maintain the random assignment table.

### Blinding

To eliminate differences between the PLC group and control group and to maintain the blinding, the NS will be administered in an identical way as the PLC. According to Yoon et al.’s study published in 2004 [32], NS is suitable as a control intervention for hominis placenta pharmacopuncture since the acupuncture sensation after injection is like that of the medication. The same amount of PLC or NS will be injected by the physician, at the same acupoints using the same gauge of syringe, so that participants do not feel any difference. Due to differences in the color of the PLC and the saline solution, the syringes will be covered with translucent tape to eliminate bias by the subjects.

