### Outcome measures

#### Primary outcome: hot flash score

The primary outcome will be the mean change in the hot flash score from baseline to 8 weeks. The hot flash score for each day will be calculated as the number of hot flashes multiplied by the average severity of the hot flashes on that day. Participants will record the number of hot flashes in a daily diary during the trial. Flashes will be scored by severity on a scale from 0 to 4 (normal 0, mild 1, moderate 2, severe 3, and very severe 4) [33]. Since the hot flash score does not have a highest value, the residual hot flash score will be used for all statistical analyses. The hot flash score measured at the baseline will be normalized to 100, and the residual hot flash score will be calculated as a percentage of the baseline score.

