Western medicine has associated climacteric symptoms with the reduced function of the hypothalamic-pituitary-gonadal axis. Conversely, traditional Korean medicine frequently attributes renal deficiency as the underlying mechanism for climacteric symptoms. The normal functions of the kidneys in Korean medicine include thermoregulation, sexuality, and water homeostasis. During the menopausal transition, kidney function may decline with increasing age. In Korean medicine, many menopausal symptoms, such as hot flashes, dry mucosa, sleep disorders, and recurrent urinary tract infections, are regarded as symptoms of a deficiency of yin in the kidneys. Yin is identified with receiving and regenerative elements. The hominis placenta is known to have the power to replenish the yin in the kidneys [46].

Despite the wide use of pharmacopuncture in Korean medicine, there are several issues with treatment. First, the efficacy of hominis placenta pharmacopuncture for the treatment of climacteric syndrome needs to be evaluated in large well-designed clinical trials. However, objectification and standardization of the medication is the first step in addressing the numerous problems inherent in operating a clinical trial on hominis placenta pharmacopuncture. We standardized the medication by using PLC manufactured following the guidelines for the Unicenta injection, after obtaining approval from the Korean Ministry of Food and Drug Administration. Unicenta is a commercially available injection. Published results of clinical trials in Korea indicate that it can alleviate menopausal symptoms [47]. In Korea, hominis placenta is injected subcutaneously. It has been shown to improve menopausal symptoms and liver function.

The second problem involves blinding. In this study, the control group is administered NS, which differs in color and viscosity from PLC. Hence, medical doctors can easily identify the medication. Since this study is designed as a single-blind study, blinding of participants will be maintained by covering the syringe with opaque tape.

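### The Blinding section specifies translucent tape over the syringes and the Discussion specifies opaque tape, so the covering that protects the trial's only described blinding is contradictory

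*Protocol article*

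**What the plan says.** The trial is single-blind (Design and setting): "This will be a randomized placebo-controlled single-blind multi-center parallel-design clinical trial". The Blinding section gives the reason for covering the syringe, "Due to differences in the color of the PLC and the saline solution", and then the covering itself: "the syringes will be covered with translucent tape to eliminate bias by the subjects".

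The Discussion returns to the same problem. It says that "the control group is administered NS, which differs in color and viscosity from PLC" and concludes "Hence, medical doctors can easily identify the medication". It then says that "blinding of participants will be maintained by covering the syringe with opaque tape".

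On the primary outcome, the protocol article says "The primary outcome will be the mean change in the hot flash score from baseline to 8 weeks", and on its source, "Participants will record the number of hot flashes in a daily diary during the trial". Severity is graded from 0 to 4 under the same heading. The secondary outcomes include the Menopause Rating Scale (MRS), described as self-administered.

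**The concern.** The tape has one job, which is to stop the participant seeing a color difference that the article itself reports. The Methods text, which describes how the trial is run, names a material that transmits light. The Discussion names one that does not. Anyone who follows the Blinding section literally could leave the color discernible at every injection visit.

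What is at stake is the internal validity of the primary comparison. Participant masking is the only blinding the article describes, and the participant produces the primary endpoint. If she forms a belief about her allocation, her expectation can affect both the number of flashes she records and the severity that goes into the score, and likewise her MRS answers. A bias of this kind is not reduced by a larger sample, and none of the analyses described in the article would remove it.

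**Working it through.** No arithmetic applies. No figure in the plan depends on the tape, and changing the word alters no sample size, power or significance level. The check is a comparison of the texts.

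**1. Do the two statements concern the same object?** Yes. Each describes a tape covering on the syringe, and each gives participant blinding as its purpose.

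| | Blinding section | Discussion |
|---|---|---|
| Difference to be hidden | color | color and viscosity |
| Covering | translucent tape | opaque tape |
| Purpose | avoid bias by the subjects | keep participants blinded |

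The purpose agrees and the material does not. Neither statement belongs to an amendment log or a description of superseded text, and nothing elsewhere in the article reconciles them.

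**2. Is another visual safeguard described?** No. The Blinding section also requires equal volume, the same acupoints and the same gauge, and it cites an earlier study on the sensation after injection. These measures make the injections feel alike. Only the tape deals with what can be seen.

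**3. Who is blinded?** The design is single-blind, and the Discussion accepts that doctors can tell the two solutions apart. The Interventions section has the materials labelled by name. That leaves the participant as the only blinded party described.

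**4. How often is the syringe in view?** Design and setting gives 16 injections (twice a week for 8 weeks). The Abstract gives 18 sessions over 9 weeks, and the visit schedule marks treatment at visits 2 to 18. On any of these counts exposure is repeated many times.

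**5. Does the blinded party generate the endpoint?** Yes. The daily hot flash score is the diary count multiplied by the average severity for that day. The MRS is also completed by the participant.

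**6. What follows?** If the Blinding section is applied as written, a known color difference sits behind a material that cannot be relied on to conceal it, in front of the person who reports the outcome. If the Discussion is applied, the stated purpose of the tape is met. The article does not show which of the two happens at the sites.

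**The case against.** The strongest reply is that this is a slip in one adjective. The sentence that says translucent also gives the aim of eliminating bias by the subjects, and the Discussion says opaque outright. This largely stands: nothing shows that see-through tape was chosen deliberately, so the point is an internal contradiction and not a defective design decision. It does not settle the matter, because the weaker word is in the Methods text. Protocol version 1.9, cited under Trial status, is not shown, so its wording and the sites' practice are unknown.

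A reader might infer that translucent tape leaves the color plainly visible and so unblinds participants. The document does not support that. Translucent tape may blur a color, and the article gives no tape specification, no color for PLC and no indication of how strong the contrast is. In a parallel design each woman also receives only one solution, so she cannot compare the two and must still link a color to an arm. The article does not say what participants are told. The supportable statement is that such tape cannot be relied on to hide the color.

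A reader might also try to put a size on the bias. For example, suppose half the women recognize their solution and the expectation gap is 10 to 20 points of residual score. That gives 0.5 × 10 = 5 to 0.5 × 20 = 10 points, or 25% to 50% of a 20-point planning difference. This is purely hypothetical. Neither the recognition rate nor the gap comes from the document, and reading the 20% difference in the Sample size section as 20 points of residual score is a third assumption. The figures should carry no weight.

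Finally, how much of the barrel is covered and where the syringe is filled are details that an article commonly leaves to the full protocol, so their absence is no fault here.

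**Conclusion.** The contradiction is literal and stands: the same covering is translucent in the Blinding section and opaque in the Discussion. It is more than clerical, because the wording in the Methods text undermines the tape's stated purpose, participant masking is the only blinding described, and participants report the primary outcome and the MRS themselves. The consequence is a risk of expectation bias whose size cannot be derived from the document.

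This conclusion assumes only that translucent carries its ordinary meaning of letting light through. It does not assume that any participant has been unblinded or that any site uses see-through tape. It should be settled promptly, because recruitment began on 31 October 2018 and was expected to run to the end of December 2019, and masking that has been lost cannot be restored afterwards.

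**What to change.** Change translucent to opaque in the Blinding section so that it agrees with the Discussion. Check that protocol version 1.9 uses the same word. Confirm with each of the three hospitals that the tape actually in use hides the color difference.

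The cost is one word and one query per site. The sample size, the analysis and the visit schedule are unaffected.

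Asking each woman at the end of treatment which solution she believes she received would be an optional addition. Its absence is not part of the error. In a trial already recruiting it would probably need an amendment, and it would miss women who have already finished.
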